**Table 1: Trial procedure**

| Procedure                                      | D1 | D2-13 | D14 |
|------------------------------------------------|----|-------|-----|
| Informed consent                               | x  |       |     |
| Review of eligibility criteria                 | x  |       |     |
| Randomization                                  | x  |       |     |
| Demography, medical history, comorbidities     | x  |       |     |
| Physical examination                           | x  | x*    |     |
| Clinical evaluation                            | x  | x*    |     |
| Pregnancy test in women                        | x  |       |     |
| CBC                                            | x  | x*    |     |
| dengue RT-PCR                                  | x  |       |     |
| Side effects monitoring                        | x  | x*    | x   |
| Warning signs, severe dengue, and dengue shock |    | x*    | x   |
| Admission status                               |    | x*    | x   |

\*outpatients visit at least every other day, or daily inpatient visit until recovery

## Statistical Analysis

### Sample size and power

Based on findings in a study reporting the incidence of dengue with warning signs excluding lethargy, (21) we have assumed a 54.5% event rate of the primary outcome in the standard group. Regarding the 22% absolute risk reduction in dengue shock syndrome in an open-label study, (20) we have assumed a 15% effect size for the intervention (absolute risk reduction of 0.15). With a 5% rate of loss to follow-up, and a one sided test at the 2.5% level, a sample size of 358 provides approximately 80% power to detect a reduction in the primary endpoint between the two arms.

### Outcomes

The **primary objective** is to provide reliable estimates of the effect of montelukast on the incidence of dengue warning signs, which will be assessed during the defined period, 14 days or until the discontinuation of the follow up appointment by the attending physicians, whichever is shorter. Those who missed the follow-up appointment will be recorded as missing values after the time of the last known status.

The **secondary objectives** are to assess the effects of montelukast on components of composite outcomes of dengue with warning signs, hospitalization, length of hospital stay, severe dengue, dengue shock, and mortality.

### Methods of analysis

Comparisons will be made between all participants randomized to the different treatment arms, irrespective of whether they received their allocated treatment (“intention-to-treat” analyses).

The primary analysis will apply Cox proportional hazards regression to all randomized participants to compare the time from randomization to the first occurrence of dengue with warning signs between the two treatment groups. The model will include an indicator for intervention arm as its sole predictor variable. Clinical site at randomization will be a stratifying factor. Follow-up time will be censored at the last date of event ascertainment. The p-value from the primary analysis will be based on the chisquare statistic from a likelihood ratio test obtained from proportional hazards models with and without the term for intervention arm. This likelihood ratio test will constitute the primary test of statistical significance for the primary analysis. Tests of heterogeneity or trend will generally be used to assess disparity in efficacy among different subgroups (e.g. men vs. women; age group, high vs. low viral load, dengue serotypes). One sided tests at the 0.025 level are used.

The secondary analysis will be analyzed using chi-square test or Fisher exact test for categorical variables, and Student T-test or Wilcoxon rank-sum test for continuous variables. These will be reported with 95% confidence intervals and nominal p-values.

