### **Baseline Information**

Once local regulatory requirements have been approved, investigator plans to identify potential study patients may be implemented. Participant informed consent must also be obtained prior to performing any procedures related to the trial. The following key elements are outlined in the study assessments and procedures below:

1. Verify participant's interest in study.
2. Obtain study consent
3. Continue collection of screening information, including such items as contact information, additional eligibility information, and medical history.
4. Confirmation that all inclusion/exclusion criteria satisfied
5. Completion of the study randomization procedure and baseline data collection

The following information will be recorded on the case record form by the attending clinicians:

- Patient details (e.g. date of birth, sex, weight)
- Dengue symptom onset date
- Major comorbidity (e.g. heart disease, diabetes, chronic lung disease)
- Date of hospitalisation
- Laboratory results
- Dengue serotypes
- Name of person completing the form

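### The primary Cox model, stratified by site, leaves out every other baseline covariate although likely prognostic ones are already collected: a missed gain in efficiency, not an error

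*Protocol*

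**What the plan says.** Under Methods of analysis, the primary analysis is a Cox regression of time from randomization to first warning sign in all randomized participants. The protocol states: "The model will include an indicator for intervention arm as its sole predictor variable". It then adds: "Clinical site at randomization will be a stratifying factor". The p-value comes from a likelihood ratio test "obtained from proportional hazards models with and without the term for intervention arm", and "One sided tests at the 0.025 level are used". No reason is given for leaving out other baseline variables.

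Elsewhere the protocol plans to collect variables that could serve as covariates. The Baseline Information list includes "Dengue symptom onset date", date of birth and laboratory results. Table 1 schedules "Demography, medical history, comorbidities" and a CBC on day 1. Under Primary Hypothesis, one of the six composite components is a rise in haematocrit together with a fall in platelets.

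For the sample size, the protocol states: "we have assumed a 54.5% event rate of the primary outcome in the standard group". It sets an absolute risk reduction of 0.15 and 5% loss to follow-up, and arrives at 358 patients for approximately 80% power.

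**The concern.** The clock starts at randomization, not at symptom onset, and the eligibility criteria set no limit on days since onset. Patients can therefore enter at somewhat different stages of illness and still share one time axis. Day-1 haematocrit and platelets are the starting values for one endpoint component. It is plausible that these variables, and age, help to predict who develops a warning sign and when.

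In a Cox model, omitting a prognostic covariate pulls the treatment hazard ratio towards 1 and costs power, even when randomization has balanced the covariate. Randomization is stratified by centre alone, so chance imbalance in day of illness is not controlled by design or by the model. The protocol fixes the model explicitly, so a later analysis plan could not add covariates to the primary test without contradicting it. At stake is some power at an unchanged sample size.

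**Working it through.** **Inputs from the protocol.** Event rate 54.5% on placebo; 54.5% − 15% = 39.5% on montelukast; one-sided level 0.025; power 80%; 5% loss to follow-up.

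**Reproducing 358.** Two proportions with unpooled variance:

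n per arm = [p1(1−p1) + p2(1−p2)] × (z0.975 + z0.80)² / 0.15² = [0.545 × 0.455 + 0.395 × 0.605] × (1.960 + 0.842)² / 0.0225 = 169.9, so 170.

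Total 340; 340/0.95 = 357.9, so 358. The stated figure is reproduced exactly. The formula assumes no covariate adjustment.

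**Power of the planned arm-only Cox test.** Under proportional hazards the implied hazard ratio is ln(0.605)/ln(0.455) = 0.638. Expected events among 340 evaluable patients are 340 × (0.545 + 0.395)/2 = 159.8. Schoenfeld's formula gives √(159.8/4) × |ln 0.638| − 1.96 ≈ 0.88, which is 81.0% power. The planned test meets its own target before any allowance for interim looks.

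**Power with adjustment.** The protocol does not say how strongly the baseline variables predict the outcome, so this is an assumption. Each scenario used 3,000 simulated trials of 340 patients, exponential event times over the 14 days, site ignored, and marginal risks held at 54.5% and 39.5%. One standard-normal baseline score stood for the combined covariates. The test was the signed likelihood ratio at 1.96, with and without the score in both models.

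| Assumed log-hazard SD of score | Arm only | Adjusted | Gain (points) | Adjusted HR |
|---|---|---|---|---|
| 0 | 81.0% | 81.0% | 0 | 0.634 |
| 0.3 | 80.3% | 82.8% | 2.6 | 0.629 |
| 0.5 | 80.7% | 85.5% | 4.7 | 0.617 |
| 0.7 | 81.0% | 90.1% | 9.1 | 0.593 |

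Gains were computed before rounding. The unadjusted hazard ratio stayed at about 0.63 to 0.64 throughout. A run at SD 1.0 gave 83.0% against 96.4%, but I place no weight on so strong a predictor. Type I error was 0.021 to 0.030 for both models, with a simulation standard error of √(0.025 × 0.975/3000) ≈ 0.003.

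**A less favourable case.** The table adjusts for the exact score that generated the data. When the fitted covariates carried only half the prognostic variance, the gains fell to about 0, 2.5 and 5 points at SD 0.3, 0.5 and 0.7.

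**The case against.** The strongest reply is that nothing here is wrong. The arm-only test is prespecified, respects the only randomization stratum, holds its type I error and reaches the planned power. Wanting more power than planned is a preference. That stands: this is an improvement on offer, not a defect in validity.

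The second reply is that the gain rests wholly on an assumed prognostic strength. That one of six components is a change in haematocrit and platelets does not show that day-1 values predict the composite. The protocol also narrows the spread in illness stage: it aims at early infection, excludes anyone with a warning sign, and requires enrolment within 24 hours of a positive NS1 test. An effect of onset day need not be linear either. All of this stands, and it is why the result is a range starting at zero.

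The third reply is that adjustment changes what is estimated. The sample size is built on a marginal risk difference, whereas an adjusted hazard ratio is conditional. That also stands, and is met by reporting the marginal risk difference alongside.

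Several stronger readings are tempting but unsupported:

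- A reader might infer that the plan excludes all covariates. It does not, since site is a stratum.
- A reader might infer that the primary test is invalid or that the trial falls short of its stated power. The check above shows neither.
- A reader might expect adjustment to make up for the power lost to the two interim looks. That loss was not calculated here, so no such offset can be claimed.
- Adjustment is not wholly free: no new data are needed, but functional form and missing baseline values have to be settled.

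**Conclusion.** The point holds as a missed efficiency gain. The primary model uses site but no other baseline variable, although days from onset, age and day-1 counts can be derived from data already planned. At the same sample size, adjustment would add 0 to about 9 power points for an assumed log-hazard SD of 0 to 0.7, and about half that if the fitted terms capture half the prognostic variance.

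The direction is secure: in the simulations, adjustment cost no power when the score was useless, and type I error was preserved. The size is not secure, because nothing in the protocol places the trial within the assumed range. The figures also rest on proportional hazards, 340 evaluable patients and no allowance for interim looks.

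**What to change.** Before unblinding, amend Methods of analysis so that the Cox model keeps site as a stratum and includes days from symptom onset to randomization, day-1 platelet count, day-1 haematocrit and age. Put these terms in both models of the likelihood ratio test, so that the test still isolates the arm. State the functional form of each term and a simple rule for missing baseline values. Report the arm-only model as a sensitivity analysis, with the marginal risk difference alongside. If the sponsor prefers to keep the arm-only model as primary, the protocol should give the reason.

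The cost is protocol and analysis-plan wording. No procedure, visit or patient is added, and four terms against about 160 expected events is a light burden. The downside is that the hazard ratio becomes conditional on the covariates and must be described as such.

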### **Administration of allocated treatment**

Study medication will be given 10 mg orally immediately and every day thereafter for 10 days or until recovery, defined as the discontinuation of the follow up appointment by the attending physicians, whichever is shorter.

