### **Collecting follow-up information**

The following information will be ascertained at least every other day for 14 days or until the discontinuation of the follow up appointment by the attending physicians, whichever is shorter.

- Clinical symptoms and signs of warning signs

- Hospitalisation status, death status
- Laboratory results

Follow-up information is to be collected on all study participants, irrespective of whether or not they complete the scheduled course of allocated study treatment. Study staff will seek follow-up information through various means including medical staff, reviewing information from medical notes, routine healthcare systems, and registries.

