#### **Duration of follow-up**

All randomised participants are to be followed up until the discontinuation of the follow up appointment by the attending physicians, whichever is shorter. It is recognised that in the setting of this trial, there may be some variability in exactly how many days post-randomisation information on disease status is collected. This is acceptable and will be taken account of in the analyses and interpretation of results, the principle being that some information about post-randomisation disease status is better than none.

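### The primary Cox model censors patients when the physician ends follow-up at recovery, so the hazard ratio need not reflect 14-day incidence if the drug changes recovery time; Table 1 implies a day-14 assessment for everyone.

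*Protocol*

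**What the plan says.** All references are to the protocol.

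- **Methods of analysis.** The primary Cox regression is to "compare the time from randomization to the first occurrence of dengue with warning signs between the two treatment groups". The censoring rule is "Follow-up time will be censored at the last date of event ascertainment".
- **Outcomes.** Warning signs are assessed for "14 days or until the discontinuation of the follow up appointment by the attending physicians, whichever is shorter". The stated objective is the effect on the incidence of warning signs.
- **Collecting follow-up information.** Data are gathered "at least every other day for 14 days or until the discontinuation of the follow up appointment by the attending physicians".
- **Duration of follow-up.** The rule given here reads: "All randomised participants are to be followed up until the discontinuation of the follow up appointment by the attending physicians, whichever is shorter". Only one limit is named, so there is nothing for it to be shorter than. The section accepts variable follow-up and promises to allow for it in the analysis, without saying how.
- **Administration of allocated treatment.** Treatment may run "until recovery, defined as the discontinuation of the follow up appointment by the attending physicians". The event that ends follow-up is thus, by definition, recovery.
- **Table 1.** The row "Warning signs, severe dengue, and dengue shock" is marked at D14, as are admission status and side effects. None of these D14 marks carries the asterisk that limits the D2–13 visits to the time before recovery. Physical examination and CBC are not marked at D14.
- **Sample size and power.** The trial is sized on proportions: 54.5% in the standard group and an absolute reduction of 0.15.

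**The concern.** Censoring in a Cox model is harmless when the censored patient has the same future risk as those still under observation. Here the usual reason for censoring is recovery, which largely ends the risk of a warning sign. Each patient who recovers event-free leaves the risk set, and those who remain are increasingly the patients about to have an event.

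If recovery takes equally long in both arms, this happens symmetrically. If montelukast changes recovery time, the risk sets become unbalanced and the hazard ratio moves even when 14-day incidence does not. Blinding does not prevent this, because the censoring follows the patient's own course. The primary test could then understate or overstate the effect on the quantity named in the objective. If day-14 status is never collected, the data cannot fully repair it later.

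**Working it through.** **1. The plan's own figure.** With p1 = 0.545, p2 = 0.395, one-sided 0.025 and 80% power, the unpooled two-proportion formula gives

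n per arm = (1.960 + 0.842)² × (0.545×0.455 + 0.395×0.605) / 0.15² = 169.9, so 170.

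Two arms make 340, and 340/0.95 = 357.9, so 358. The plan's number is reproduced, and it is a calculation for incidence. (The pooled formula gives 173 per arm, and 346/0.95 rounds up to 365.)

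**2. The mechanism in one risk set.** Illustrative assumptions: 170 patients per arm, the same 54.5% risk in both, 10 patients per arm still to have a warning sign at day 6, and recovery time normal with SD 2 and mean day 5 (control) or day 6 (drug). Event-free patients number 170 × 0.455 = 77.35 per arm.

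- Control: 30.9% have not yet recovered, so 23.9 remain. Hazard = 10/(10 + 23.9) = 0.295.
- Drug: 50% have not yet recovered, so 38.7 remain. Hazard = 10/(10 + 38.7) = 0.205.
- Ratio = 0.205/0.295 = 0.70, with no difference in incidence.
- With recovered patients kept in: 10/(10 + 77.35) = 0.114 in both arms, ratio 1.

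**3. Size for the whole trial, by simulation.** Inputs from the protocol: 54.5%, 39.5%, one-sided 0.025, and 340 evaluable (358 × 0.95). Assumed, because the protocol gives none: time to warning sign gamma with mean day 3 or 4 and SD 1.5; recovery SD 2; times rounded up to whole days; nobody destined for a warning sign is discharged before it. Log-rank test, 3,000 runs per row.

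| Mean recovery day, control v drug | Truth | Quantity | Events at mean day 3 | Events at mean day 4 |
|---|---|---|---|---|
| 7 v 7 | equal risk | false benefit | 2.2% | 2.1% |
| 7 v 8 | equal risk | false benefit | 3.8% | 5.2% |
| 5 v 6 | equal risk | false benefit | 8.3% | 13.4% |
| recovered kept to day 14 | equal risk | false benefit | 2.9% | 2.0% |
| 7 v 7 | 54.5% v 39.5% | power | 79% | 78% |
| 9 v 8 | 54.5% v 39.5% | power | 75% | 73% |
| 7 v 6 | 54.5% v 39.5% | power | 65% | 56% |
| 7 v 5 | 54.5% v 39.5% | power | 44% | 22% |
| recovered kept to day 14 | 54.5% v 39.5% | power | 79% | 78% |

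Other sets of runs, including one using the site-stratified Cox likelihood ratio test that the protocol plans, moved these results by a few points. The ranges in the verdict span all of them. Equal recovery leaves type I error alone wherever it falls. It leaves power near the design value at day 7, but gave about 70% when both arms recover at mean day 5 and events occur at mean day 4.

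**4. A separate model, for the mismatch of scales only.** With constant hazards λ (event) and μ (recovery), 14-day incidence is λ/(λ+μ) × (1 − exp(−14(λ+μ))). Take μ = 0.10 and λ = 0.1311 per day: incidence is 54.5%. Multiply only μ by 1.5: incidence falls to 45.7%, while the Cox hazard ratio stays exactly 1. That ratio correctly describes the event hazard, but it is not the incidence the objective names.

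**The case against.** - **Timings are assumed.** True. The large biases need patients to be discharged while warning signs are still arising. The protocol allows up to 14 days of follow-up, so later discharge is quite compatible with it, and the bias is then small. This stands and is why the size is given as a range. But the protocol sets no minimum follow-up, so late discharge is not assured.
- **False benefit needs a drug that delays recovery without affecting warning signs.** Nothing in the protocol suggests this. The likelier direction, earlier recovery, costs power and works against the drug. This stands.
- **Table 1 already solves it.** If D14 is carried out for everyone, the last ascertainment is day 14 and the problem largely disappears. But three sections of text say otherwise, so staff cannot tell which governs.
- **The SAP may handle it.** Competing-event or sensitivity methods may sit there. The protocol, however, does not leave the point open: it fixes the censoring rule and the follow-up window that together create the problem.
- **A cause-specific hazard is a legitimate estimand.** Agreed, but it fits the stated incidence objective and sample size less well.

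A reader might infer that the primary test has an inflated type I error or is invalid as it stands. The documents do not support that: a drug with no effect on either recovery or warning signs is tested at the nominal level.

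**Conclusion.** The point holds as a conditional bias combined with an unreconciled conflict between text and table. Patients who recover event-free are censored informatively, and the hazard ratio need not track 14-day incidence.

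For a one-day difference in recovery, with warning signs at mean day 3 to 4 and 340 evaluable patients:

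- one-sided false benefit is 3–6% (day 7 v 8) to 8–16% (day 5 v 6);
- power is 72–76% (day 9 v 8) to 52–68% (day 7 v 6).

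A two-day difference (day 7 v 5) lowers power to 19–44%. Keeping recovered patients at risk gives about 2.5% and 77–80%.

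These figures depend on timings that the protocol does not state and on a drug effect on recovery time. They are not predictions. This should be fixed; the evidence does not make it a fatal flaw.

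**What to change.** 1. **Collecting follow-up information, Duration of follow-up, Outcomes.** Reconcile these with Table 1 so that the outcome window is 14 days for every patient. Seek D14 status through the Table 1 assessment or through the notes, routine systems and registries that the protocol already allows. This concerns ascertainment only, not treatment duration.
2. **Methods of analysis.** Keep patients discharged as recovered without a warning sign at risk as event-free to day 14 unless a later event is found, including those with no D14 contact. Censor early only for follow-up missed before recovery or for withdrawal of consent.
3. **Sensitivity analysis.** Censor recovered patients who could not be contacted at D14 at their discharge date.
4. **Reporting.** Give the day-14 cumulative incidence in each arm and the risk difference beside the hazard ratio.

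Cost: wording changes and one D14 status check that Table 1 already implies. N = 358 is unchanged. The downside is that, for some recovered patients, the components needing examination or blood tests (liver enlargement, haematocrit with platelets) are assumed absent at day 14 rather than measured, since Table 1 schedules neither then.

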### **Randomization and allocation concealment**

Eligible patients will be randomized using a computer-generated randomisation list prepared by an independent statistician and stratified by the centre with a block size of four in a 1:1 ratio to one of the two treatment arms:

Arm 1: montelukast 10 mg

Arm 2: placebo 10 mg

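### The primary test is a non-directional likelihood-ratio chi-square declared one-sided at 0.025, with no rule for making its p-value one-sided

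*Protocol*

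**What the plan says.** Three parts of the protocol's Statistical Analysis chapter bear on the primary decision rule.

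- **Methods of analysis.** The primary analysis is a Cox model stratified by site, with treatment arm as the only covariate. "The p-value from the primary analysis will be based on the chisquare statistic from a likelihood ratio test obtained from proportional hazards models" (arm term included versus omitted), and this is named as the primary test of significance. The paragraph then turns to subgroup heterogeneity and trend tests, and ends "One sided tests at the 0.025 level are used".
- **Sample size and power.** The trial is sized for "a one sided test at the 2.5% level", and "a sample size of 358 provides approximately 80% power to detect a reduction in the primary endpoint between the two arms".
- **Data and safety monitoring board.** Interim analyses are planned at 50% and 75% of enrollment, using a Lan-DeMets spending function of O'Brien-Fleming type, with alphas of 0.006, 0.018 and 0.026 for the two interim looks and the final look. The section does not say whether these are one-sided or two-sided, or whether they are increments of alpha spent or nominal p-value thresholds.

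No part gives a sign condition, a halving rule or a signed root for the likelihood-ratio statistic.

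**The concern.** A one-degree-of-freedom likelihood-ratio chi-square measures how far the hazard ratio lies from 1, not on which side. At equal information, a hazard ratio of 0.6 and one of 1/0.6 give the same statistic and the same p-value. That p-value is two-sided in effect. The protocol names it as the primary p-value and attaches a one-sided level of 0.025 to it. The statistic and the level do not fit together without a further step, and the step is not given.

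What is at stake is which results count as positive. Two competent analysts could take the same data and the same protocol and reach opposite conclusions whenever the chi-square p-value lies between 0.025 and 0.05 and the hazard ratio is below 1. If the choice is made after the data are seen, the result can drive the choice.

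**Working it through.** **Inputs**

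- Control event rate 0.545: "we have assumed a 54.5% event rate of the primary outcome in the standard group" (Sample size and power).
- Absolute risk reduction 0.15 (same section), so the montelukast rate is 0.395.
- Loss: "With a 5% rate of loss to follow-up" (same section).
- Allocation 1:1: "with a block size of four in a 1:1 ratio to one of the two treatment arms" (Randomization and allocation concealment).
- Level: one-sided 0.025 (Sample size and power; Methods of analysis).

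**Step 1. Reproduce the stated sample size.** For two proportions with unpooled variance:

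variance term = 0.545 × 0.455 + 0.395 × 0.605 = 0.48695

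n per arm = (1.960 + 0.842)² × 0.48695 / 0.15² = 169.9, so 170 per arm and 340 in total

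340 / 0.95 = 357.9, so 358. This matches the protocol.

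**Step 2. Power under the two readings, ignoring interim looks.** With 170 evaluable patients per arm, the expected Z is

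θ = 0.15 / √(0.48695 / 170) = 2.803

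| Reading | Level in benefit direction | Critical Z | Power |
|---|---|---|---|
| Chi-square p signed or halved, then compared with 0.025 | 0.025 | 1.960 | Φ(2.803 − 1.960) = 80.0% |
| Chi-square p compared with 0.025 as it stands | 0.0125 | 2.241 | Φ(2.803 − 2.241) = 71.3% |

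Other approximations at 340 evaluable patients agree. For the event-driven methods, proportional hazards implies a hazard ratio of ln(0.605)/ln(0.455) = 0.638, with about 160 events.

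| Method | Signed or halved | As it stands |
|---|---|---|
| Pooled variance | 79.4% | 70.4% |
| Schoenfeld | 81.0% | 72.5% |
| Freedman | 79.7% | 70.9% |

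To regain 80% under the second reading would take (2.241 + 0.842)² × 0.48695 / 0.0225 = 205.7, so 206 per arm; 412 / 0.95 gives about 434 randomized.

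**Step 3. Do the interim alphas settle the reading?** The three values sum to 0.006 + 0.018 + 0.026 = 0.050. They agree with the increments of 2[1 − Φ(z₁₋α/₂ / √t)] at t = 0.5, 0.75 and 1 with α = 0.05, which are 0.0056, 0.0181 and 0.0264. A total of 0.05 would suit chi-square p-values judged at 0.05 overall, but the text declares 0.025 and does not say that this is meant.

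If the values are instead applied as nominal thresholds at each look, taking information as proportional to enrollment and θ = 2.803 at full information:

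| P-value compared with the alphas | Critical Z at the three looks | Overall error in benefit direction | Power |
|---|---|---|---|
| Unhalved chi-square p | 2.748, 2.366, 2.226 | 0.018 | about 74% |
| One-sided p | 2.512, 2.097, 1.943 | 0.035 | about 82% |

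Neither row gives the declared 0.025. The first falls short of it and the second exceeds it.

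**Step 4. A design that does hold one-sided 0.025.** A Lan-DeMets O'Brien-Fleming-type spending function with total 0.025 and looks at 50%, 75% and 100% spends 0.0015, 0.0097 and 0.0250 cumulatively. Critical values are 2.963, 2.359 and 2.014, with nominal one-sided levels 0.0015, 0.0092 and 0.0220. Power with 340 evaluable patients is about 79%.

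**The case against.** A reader might infer that the true one-sided level is 0.0125 and that the trial has only about 71% power. The protocol does not support that as a statement of fact. It says that the p-value is based on the chi-square and declares a one-sided 2.5% test in two sections; nowhere does it say that the unhalved p-value is set against 0.025. A one-sided test can be built on this statistic by taking its signed root, and power then stays at about 80% with 358 patients. The 0.0125 and 71% are the consequence of one reading. That reading is also conservative and would not inflate false claims of benefit.

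Nor should it be said that a harmful result would be claimed as a success. The protocol calls the trial a superiority trial and asks whether montelukast reduces warning signs, so the intended direction is clear even though the test rule omits it.

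The closing one-sided sentence does not say that it covers the heterogeneity and trend tests; that is an inference from where it stands. A trend test or a two-level comparison, such as men against women, could be signed. Only comparisons across more than two levels, such as serotypes, have no direction.

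Finally, converting a test statistic to a one-sided p-value is often left to the statistical analysis plan, which is not at hand. That would answer a plain omission. Here, however, the protocol itself fixes the statistic, the source of the p-value, the sidedness and the level, and these do not fit together as written. That part of the concern stands.

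**Conclusion.** The point holds as an ambiguity in the primary decision rule, not as a proven loss of power. The protocol pairs a non-directional chi-square with a one-sided 0.025 level and gives no conversion. Depending on the reading, the level in the benefit direction is 0.025 or 0.0125, and fixed-design power is about 80% or about 71% (70.4% to 72.5% across methods). Results with a chi-square p-value between 0.025 and 0.05 and a hazard ratio below 1 change sides. The interim alphas leave the question open and, used as nominal thresholds, give a one-sided error of 0.018 or 0.035 in place of 0.025.

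The figures rest on the protocol's own event rates, 340 evaluable patients and a normal approximation. The 80% and 71% leave out the interim looks. The group-sequential figures assume that information accrues in proportion to enrollment.

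**What to change.** In Methods of analysis, keep the Cox model and the likelihood-ratio test and add the rule that makes the test directional:

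- Define Z = sign(log HR) × √(likelihood-ratio chi-square), with HR as montelukast against placebo. Declare superiority only if HR < 1 and Z is at or below minus the critical value for an overall one-sided 0.025.
- Give that value. It is 1.96 without interim looks, which is the same as a chi-square p-value below 0.05 with HR < 1. It is 2.014 at the final look for a one-sided 0.025 Lan-DeMets O'Brien-Fleming-type design with looks at 50% and 75%.
- In the Data and safety monitoring board section, restate the alphas on the same one-sided scale with a total of 0.025, and say whether they are cumulative spend, increments or nominal levels.
- Limit the one-sided wording to the primary test, and make the heterogeneity tests ordinary chi-square tests.

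This takes a few sentences in two sections. The sample size stays at 358; with the interim looks included, power is about 79%. The rule should be fixed before any unblinded comparison of the arms.
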